**Methods:**

In this randomized controlled trial, 308 mothers will be recruited from the antenatal clinics and postnatal wards of two major public hospitals in Hong Kong. Participating mothers will be randomly assigned into intervention and control groups. Mothers in the intervention group will be given free access to a technology-based injury prevention program with anticipatory guidance, whereas mothers in the control group will be given a relevant booklet on parenting. The injury prevention program, available as a website or on a mobile app, includes behavioral components based on the Theory of Planned Behavior. The primary outcome measure will be the change in the mother’s knowledge of child safety. The secondary outcome measures will be age-appropriate domestic safety knowledge, attitudes, intentions, perceived behavioral control, and self-reported behavior related to home safety practice. We will also determine dose-response relationships between the outcome measures and the website and mobile app usage.

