## Methods

### Study Design

This study will be a randomized controlled trial of the effectiveness of a technology-based injury prevention program for enhancing mothers’ knowledge of child safety (Figure 1). Mothers will be recruited from the antenatal clinics and postnatal wards of two major public hospitals in Hong Kong: Kwong Wah Hospital and Queen Mary Hospital. Between October, 2016 and January, 2017, nurses will identify potential participants. An experienced research assistant will provide the participants with an information sheet explaining the study, along with a consent form. The inclusion criteria will include mothers attending the antenatal clinics or staying in the postnatal wards at Kwong Wah Hospital or Queen Mary Hospital. The exclusion criteria will include subjects unable to read Chinese, and those without Internet access.

Participants will be randomly allocated into the intervention and control groups in a 1:1 ratio. All participants will be given an information pack consisting of a parenting booklet from the Maternal and Child Health Centers (MCHC). This booklet is publicly available and provides brief and general home safety tips for mothers with children under 3 years of age. The intervention group will also be given an additional leaflet containing a brief introduction to the Internet-based domestic safety platform, and instructions on how to access the website. Mothers can easily access this practical online parenting resource through the website or a mobile app. The online resource contains information on various safety topics and educational materials, including general and age-appropriate injury prevention measures suitable for mothers with infants and children between 2 and 18 months of age. Participants in the intervention group will be periodically contacted by telephone and electronic messaging to encourage them to access and engage with the domestic safety website. The research team will provide technical support to all participants who encounter problems accessing the intervention website or mobile app. Apart from technical support, no other intervention will be provided to those accessing the website or mobile app by any therapist, nurse, care provider, or physician. The control group will receive only the MCHC parenting booklet.

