All consenting participants will be asked to complete a general safety questionnaire at the antenatal clinic or postnatal ward of the two hospitals. Age-appropriate safety knowledge, attitudes, intentions, perceived behavioral control, and self-reported behavior related to home safety practice will be assessed at specific child developmental ages at 2, 6, 9, 12, and 18 months. Participants in the intervention group will be given immediate feedback on their specific injury prevention behaviors prompted by the *at-risk* (incorrect) answers obtained from their completed questionnaire. This online feedback counseling approach aims to educate mothers and enhance their awareness related to domestic injury prevention. At the end of the counseling session, each intervention participant will be provided with age-appropriate safety information. Participants’ general safety knowledge will be reassessed when their children reach the age of 18 months. Intervention participants will be reminded by telephone and email to complete the age-appropriate safety questionnaires at each developmental stage, and the final general safety questionnaire. Control group participants will be contacted using the same schedule, to remind them to read the booklet and to complete the questionnaires.

This study is registered with Clinicaltrials.gov (Identifier: NCT02835768) and has been approved by the Institutional Review Board of Hong Kong University and Hospital Authority Hong Kong West Cluster (Reference number: UW 15-465). All participants will provide written informed consent.

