### Sample Size Calculation

With reference to a computer-based parenting intervention for child injury prevention that reported a small to medium effect (d=0.42) for knowledge change [21], 92 subjects will be needed for this intervention study to detect an effect with 80% power and a 5% significance level. Assuming a 40% attrition rate between preevaluation and postevaluation, at least 154 participants should be recruited to each of the intervention and control groups.

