### Data Analysis

Changes in participants’ knowledge of child safety will be studied by comparing their knowledge before and after completing the injury prevention program, and by comparing the participants’ knowledge of child safety in the intervention and control groups. Regression analysis will be used to examine the intervention effectiveness, adjusted for participant demographics (eg, gender, age, and socioeconomic status of the parent). Data will be analyzed by an intent-to-treat approach to address loss of any follow-up data. Independent sample t-tests will be used to examine the between-group differences in age-appropriate safety knowledge, attitudes, intentions, perceived behavioral control, and actual behavior related to home safety practice. Dose-response relationships between the outcome measures and the website and mobile app usage will be determined by correlation analysis. Website and mobile app usage data will be summarized based on the number of users and their time spent using these resources during the entire intervention period. A summary of the user acceptance evaluation will be compiled to improve and develop the website and mobile app.

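### Independent t-tests are named for five secondary outcomes collected at five ages, with no age or overall contrast fixed and no use of hospital, enrolment score or a mother's other assessments

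*Protocol article*

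**What the plan says.** The Abstract lists five outcomes: "The secondary outcome measures will be age-appropriate domestic safety knowledge, attitudes, intentions, perceived behavioral control, and self-reported behavior related to home safety practice". Study Design says that they "will be assessed at specific child developmental ages at 2, 6, 9, 12, and 18 months". Data Analysis then assigns the method: "Independent sample t-tests will be used to examine the between-group differences in age-appropriate safety knowledge, attitudes, intentions, perceived behavioral control", and behaviour.

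Four other statements bear on the point:

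- Study Design has every consenting mother complete a general safety questionnaire at recruitment.
- Randomization and Masking stratifies allocation by hospital.
- Data Analysis plans a regression adjusted for demographics to examine intervention effectiveness, without saying whether this covers the secondary outcomes. It also names intention-to-treat as the answer to lost follow-up, without giving a mechanism.
- Sample Size Calculation expects substantial loss: "Assuming a 40% attrition rate between preevaluation and postevaluation, at least 154 participants should be recruited to each of the intervention and control groups".

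**The concern.** The article fixes a two-group, one-value-per-mother test for outcomes that each mother supplies up to five times. Three consequences follow.

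- **The target is open.** With no age or overall contrast named, a difference at any age on any outcome could be presented as the effect. These outcomes carry a claim: Measures makes improving them a study aim, and Results expects the intervention group to do better on all five.
- **Missing assessments are not addressed by the test.** Intention-to-treat settles the arm in which a mother is analysed, but it does not supply a value that she did not give. A t-test has no place for a mother with no value, and it cannot borrow from her other ages.
- **Design information goes unused.** Hospital and the enrolment general safety score are both available, and the test takes neither.

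At stake is whether a statement that the program improves attitudes, intentions, perceived control or behaviour rests on a comparison fixed beforehand and on as many of the randomised mothers as possible.

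**Working it through.** **Inputs.** Five outcomes (Abstract) and five ages (Study Design). The 5% level, 80% power, d = 0.42, 40% attrition and 154 per group come from Sample Size Calculation, where they apply to knowledge change only. Two-sided testing and all correlations below are assumptions.

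**1. The plan's own figure.** The effect is the one that an earlier intervention "reported a small to medium effect (d=0.42) for knowledge change". By the normal approximation, n per group = 2 × (1.960 + 0.842)² / 0.42² = 2 × 7.85 / 0.1764 = 89. The t-based calculation gives 89.96, so 90. The stated 92 is close if read as per group, and power at 92 per group is 80.9%. Then 92 / (1 − 0.40) = 153.3, rounded up to 154 per group and 308 in all. The plan therefore expects about 92 of 154 mothers per group at the final evaluation, and 154 − 92 = 62 per group without one.

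**2. Ceiling on the number of tests.** 5 outcomes × 5 ages = 25.

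**3. Chance of at least one false positive**, with no true effect and each test at 5%:

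- 25 independent tests: 1 − 0.95^25 = 72.3%, with 25 × 0.05 = 1.25 expected false positives.
- 5 independent tests (one per outcome): 1 − 0.95^5 = 22.6%.
- 25 correlated tests, simulated with 200,000 draws and an equal correlation between ages and between outcomes:

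| Assumed correlation (ages / outcomes) | Chance of at least one |
|---|---|
| 0.3 / 0.3 | 66% |
| 0.5 / 0.5 | 55% |
| 0.7 / 0.5 | 46% |
| 0.8 / 0.8 | 29% |

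**4. Possible readings of the sentence, side by side.**

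- *One test per outcome per age.* Each test is valid in itself, but there are up to 25 and none is designated.
- *All ages pooled as rows.* Independence fails. With five equally correlated rows per mother, the variance is inflated by 1 + 4ρ, and the true error of a nominal 5% test is 2Φ(−1.96/√(1 + 4ρ)). This is 19%, 26% and 31% for ρ = 0.3, 0.5 and 0.7.
- *One age only.* That age is not named.
- *One summary per mother.* No summary is described, and it would need a rule for missed ages.

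Per-age testing is the most natural reading because the content is age-specific (Table 1). On no reading is the comparison fixed.

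**5. Missing assessments.** A mother who answers at 2 and 6 months and then stops contributes nothing to a 12-month t-test unless her value is imputed. In a mixed model her earlier answers still inform the arm comparison. The t-test on observed values needs missingness unrelated to the outcome within each arm. The model needs only missingness at random given the observed assessments and covariates.

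**The case against.** Several points on the other side stand.

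- **A reader might infer that the article prescribes 25 tests at 5%. It does not.** It does not say that one test is run per age. The 5% level appears only in the sample size sentence ("to detect an effect with 80% power and a 5% significance level") for knowledge change. Twenty-five is a ceiling.
- **A reader might infer that mothers who miss a visit are dropped. That is not written.** The sentence just before the one on t-tests declares intention-to-treat as the approach to lost follow-up. Without imputation, a mother would be lost only from the age she missed.
- **A reader might infer that repeated measurement makes the t-tests invalid.** A per-age t-test compares two randomised groups with one value per mother, and correlation across ages does not break it. The loss is in efficiency and in the handling of missing data.
- **Leaving out hospital and enrolment score causes no bias** in a randomised comparison. The secondary outcomes have no baseline of their own, and the enrolment questionnaire is a different instrument.
- **A multiplicity rule for secondary outcomes is commonly left to an analysis plan**, which is not shown here. Its absence alone is no finding.
- **The instruments complicate a longitudinal model.** Topics differ by age, the behaviour checklist is age-appropriate, and the age-appropriate questionnaire re-asks items that the individual mother got wrong at the previous stage. Raw scores are not comparable across ages or, in part, across mothers.

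What remains is that the article does not merely leave the method open: it names one. That method makes poor use of the design and does not deliver the aim stated beside it.

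**Conclusion.** The point holds in a limited form and is worth correcting. It concerns secondary outcomes and leaves the primary comparison untouched. Plain independent t-tests are a weaker choice than a covariate-adjusted longitudinal model for five outcomes collected at five ages. They do not by themselves meet the intention-to-treat aim, and the comparison that would support a claim is not fixed.

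The size depends on how the sentence is carried out. It ranges from 22.6% for five independent tests up to 72% for 25, with about 29% to 66% for 25 tests under assumed correlations of 0.8 to 0.3. These figures assume that each test is run at 5% and that no true effect exists. The correlations are not in the article.

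The 40% attrition is stated for the interval between pre-evaluation and post-evaluation. The article gives no attrition by age, so it does not show how the sample would change from one age to the next.

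**What to change.** Replace the t-test sentence with the following plan.

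- **Model.** For each of the five outcomes, fit one linear mixed model with arm, age as a category, arm × age, hospital and the enrolment general safety score. Use an unstructured within-mother covariance and all observed assessments.
- **Score.** Count only the age-specific items put to all mothers at that age, leave out the re-asked items, and standardise the score within age.
- **Contrast.** Name one per outcome: the arm difference averaged over the five ages. Show per-age differences with confidence intervals as description.
- **Multiplicity.** Either apply Holm across the five contrasts or label the secondary outcomes exploratory.
- **Missing data.** State that the analysis assumes missingness at random, and say how mothers with no assessment after randomisation are treated, since the model alone does not bring them in.

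The cost is routine modelling, an assumed linear effect of the enrolment score, the missing-at-random assumption, and a scoring rule that must be written down. Isolated single-age results would no longer count as significant.

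Holm also has a price. Its strictest step is 0.05/5 = 0.01. For a single comparison at d = 0.42 with 92 per group, power falls from 80.9% at 0.05 to 59.7% at 0.01. That d was stated for knowledge change, so this is only an illustration. Averaging over ages offsets some or all of the loss where the effect is similar at each age. With complete data and equal correlation, the variance of the average is (1 + 4ρ)/5 of that at one age, which is 0.44, 0.60 and 0.76 for assumed ρ = 0.3, 0.5 and 0.7.

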#### Age-Appropriate Safety Questionnaire

This component examines age-appropriate domestic safety knowledge, attitudes, intentions, and perceived behavioral control toward home safety practice (Table 1) [30-32]. The multiple-choice questions in the questionnaire are categorized into two sections: (1) age-specific questions, and (2) assessment questions that were answered incorrectly in the previous stage by the participant (see Multimedia Appendix 2). This targeted component is designed to reinforce safety concepts and sustain knowledge enhancement.

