#### Website and Mobile App Usage Statistics

Participants will be required to register online as a *user* to access the website and the mobile app. By logging into the system, we will be able to record all actions taken by each user, including login time, duration of website usage, and what information was accessed. The captured data can be further analyzed and used for the purpose of incentive reimbursement.

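### The dose-response analysis is an unadjusted correlation that does not separate use before an outcome from use after it, or use that helps from use that wrong answers trigger

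*Protocol article*

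**What the plan says.** In Data Analysis, the article states: "Dose-response relationships between the outcome measures and the website and mobile app usage will be determined by correlation analysis". It gives no time window, lag or covariate for this correlation. The next sentence says that usage will be summarized by number of users and by "time spent using these resources during the entire intervention period".

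Under Study Design, age-appropriate knowledge, attitudes, intentions, perceived behavioral control and self-reported behavior "will be assessed at specific child developmental ages at 2, 6, 9, 12, and 18 months". Participants' "general safety knowledge will be reassessed when their children reach the age of 18 months", which is the primary outcome and falls at the last assessment.

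The same section says that intervention participants "will be given immediate feedback on their specific injury prevention behaviors prompted by the" at-risk, that is incorrect, answers in their completed questionnaire. The section on technology-based anticipatory guidance lists feedback counseling among the components of the website and app. The Age-Appropriate Safety Questionnaire section adds that each stage's questionnaire includes "assessment questions that were answered incorrectly in the previous stage by the participant".

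On logging, the usage statistics section says that the system will "record all actions taken by each user, including login time, duration of website usage, and what information was accessed".

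**The concern.** Two separate problems arise, and neither is the familiar one that motivated mothers choose to use the platform more.

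The first is time order. Use that happens after a score was taken cannot have produced it. If one whole-period total is correlated with scores at five ages, much of the supposed dose for the early scores comes after the response. That dilutes a true relation.

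The second is reverse causation built into the design. Wrong answers lead to online counseling, and the platform records what users do, so a low score can itself generate logged use. A plain correlation adds this negative path (low score, then more use) to the positive path of interest (more use, then higher score). The result may be too small, null or negative even when use helps.

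At stake is how the dose-response result is read. The abstract announces this analysis as an aim. A null or negative coefficient could be taken as evidence that the platform does not help.

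**Working it through.** **The plan's own figure.** The article gives no number for the dose-response analysis, so there is none to reproduce.

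**Step 1: time order.** Inputs are the assessment ages of 2, 6, 9, 12 and 18 months (Study Design) and a usage window from birth to 18 months. Assume even use across the window; the article does not say this. The share of whole-period use after an outcome at age t is (18 − t)/18.

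| Outcome age (months) | Calculation | Share after the outcome |
|---|---|---|
| 2 | 16/18 | 89% |
| 6 | 12/18 | 67% |
| 9 | 9/18 | 50% |
| 12 | 6/18 | 33% |
| 18 | 0/18 | 0% |

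These are exact shares of calendar time. They are shares of use only under the even-use assumption.

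**Step 2: score-triggered use.** Three statements together create the path: wrong answers prompt feedback (Study Design), feedback counseling is part of the website and app (anticipatory guidance section), and all user actions are recorded (usage statistics section). The article does not say how much time this adds.

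**Step 3: can the sign change?** This was checked with an illustrative simulation of 200,000 mothers and five stages. All parameter values are assumptions.

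- Underlying knowledge has SD 1.
- Use in a stage = stable engagement (SD 0.5) + noise (SD 1) − g × previous score.
- Score = underlying knowledge + b × cumulative use + error (SD 0.7).
- The whole-period total also includes use triggered by the 18-month score.
- b is the true benefit of use, always positive, at 0.05, 0.1 or 0.2. g is the strength of triggering, at 0, 0.2, 0.5 or 1.0. That gives 12 settings.

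Correlations for b = 0.1:

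| g | Dose | 2 mo | 6 mo | 9 mo | 12 mo | 18 mo |
|---|---|---|---|---|---|---|
| 0 | whole period | +0.05 | +0.11 | +0.16 | +0.22 | +0.26 |
| 0 | before outcome | +0.09 | +0.14 | +0.18 | +0.23 | +0.26 |
| 0.2 | whole period | −0.21 | −0.15 | −0.10 | −0.04 | +0.01 |
| 0.2 | before outcome | +0.09 | +0.05 | +0.05 | +0.07 | +0.08 |
| 0.5 | whole period | −0.50 | −0.45 | −0.39 | −0.34 | −0.28 |
| 0.5 | before outcome | +0.09 | −0.08 | −0.14 | −0.15 | −0.14 |

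Without triggering, whole-period use keeps the right sign but dilutes the early ages. With triggering (g of 0.2 or more), whole-period use gives a negative correlation for at least one age in every setting. At g = 0.5, counting only earlier use is not enough, so adjustment for the prior score is needed as well.

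**Step 4: the primary outcome.** Change in general knowledge against use up to 18 months stayed positive in all 12 settings (+0.17 to +0.62). The unadjusted 18-month level was negative in 5 of the 12, with a range of −0.46 to +0.48. The baseline score therefore matters here too.

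**Step 5: does adjustment help?** Under the same model, adjusting use before the outcome for the previous score (baseline at 2 months) gave the right sign at every age for b = 0.1, g = 0.5. Where triggering was strongest relative to benefit, some later ages stayed slightly negative. Use since the previous assessment, with the same adjustment, was positive in all settings.

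**The case against.** The strongest objection is that the whole-period sentence describes a usage summary and nothing links it to the correlation. This stands. A reader might infer that the plan defines total time as the dose, but the article does not say so. The logs record login time and content per user, so other doses are available, and the exact window may be fixed in a fuller plan. What the article does fix is the method, a correlation with no adjustment stated. The score-triggered path weakens that method whichever window is used.

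A reader might also extend the time-order problem to the primary outcome. It does not reach that far, because general knowledge is reassessed at the last assessment.

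It is fair to say that a wrong sign is only a possibility. It depends on how strongly scores drive logged use, which is not given. Every intervention participant also receives age-appropriate information whatever her score, and that part of use is not score-triggered. Controls complete questionnaires without website or app access, so questionnaire time, including time on repeated items, need not be logged as use.

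Feedback is part of the intervention, so removing it from the main dose would remove part of the treatment. This stands, and the exclusion belongs in a sensitivity analysis.

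Finally, "Mothers will be recruited from the antenatal clinics and postnatal wards of two major public hospitals in Hong Kong", so antenatal recruits may have longer access. A reader might count this as a further bias of known size. The article gives no gestation at enrolment, longer access is not the same as more use, and use before birth but after baseline is genuine exposure for the primary change score.

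**Conclusion.** The concern holds in a limited form. A plain correlation is a poor method for this question when wrong answers prompt online feedback on a fully logged platform. It can be biased downward and may change sign. The simulation shows that this is possible under assumed values; it does not show that it is likely.

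The time-order problem is conditional on whole-period time being used as the dose. It then affects only the 2- to 12-month secondary outcomes, by the shares in the first table if use is even from birth.

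The documents do not support saying that the plan has defined a defective dose, that the sign will be wrong, or that the primary comparison is at risk. Dose-response is an additional analysis, and the randomized comparison of the two groups is unaffected. The change is worth making before analysis because it is cheap and prevents the dose window from being chosen after results are seen.

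**What to change.** Replace the correlation sentence with a definition along these lines:

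- Analyze dose-response in the intervention group only, and label it exploratory.
- Relate each outcome only to logged use before that assessment. State in advance whether this is cumulative use or use since the previous assessment; the latter is less exposed to triggering by earlier scores.
- Use regression or partial correlation adjusted for the previous stage's score. For the 2-month outcomes and the 18-month general knowledge outcome, adjust for the baseline general knowledge score.
- Report a sensitivity analysis that excludes time in questionnaire and score-triggered feedback screens.
- Keep whole-period time for the descriptive usage summary.

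The scores, login times and content accessed are already to be collected, so the cost is wording and some log processing. Early-stage estimates will be less precise because less use counts as dose. Adjustment for a single prior score may leave some bias, which is a further reason for the exploratory label.
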